## Abstract

**Introduction:**

Cervical cancer is one of the most preventable cancers yet remains a disease of inequity for people with intellectual disability, in part due to low screening rates. The ScreenEQUAL project will use an integrated knowledge translation (iKT) model to co-produce and evaluate accessible cervical screening resources with and for this group.

**Methods:**

Stage 1 will qualitatively explore facilitators and barriers to screening participation for people with intellectual disability, families and support people, healthcare providers and disability sector stakeholders (*n* ≈ 20 in each group). An accessible multimodal screening resource, accompanying supporting materials for families and support people, and trauma-informed healthcare provider training materials will then be co-produced through a series of workshops. Stage 2 will recruit people with intellectual disability aged 25 to 74 who are due or overdue for screening into a single-arm trial (*n* = 48). Trained support people will provide them with the co-produced resource in accessible workshops (intervention) and support them in completing pre-post questions to assess informed decision-making. A subset will participate in qualitative post-intervention interviews including optional body-mapping (*n* ≈ 20). Screening uptake in the 9-months following the intervention will be measured through data linkage. Family members and support people (*n* = 48) and healthcare providers (*n* = 433) will be recruited into single-arm sub-studies. Over a 4-month period they will, respectively, receive the accompanying supporting materials, and the trauma-informed training materials. Both groups will complete pre-post online surveys. A subset of each group (*n* ≈ 20) will be invited to participate in post-intervention semi-structured interviews.

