#### Main trial design

2.4.2

The main trial is a single-arm study aimed at evaluating the primary study outcome (a change in informed decision-making about cervical screening by people with intellectual disability). An accessible informed decision-making tool will be created based on existing tools and surveys informed by the research team, Advisory Group members with intellectual disability and experts in health literacy. The modified tool will collect data via interviews using a brief set of pre-intervention open-ended accessible questions across three domains: knowledge, attitudes to screening and intention to screen (49–52). The trial will serve as a pilot study for a larger appropriately powered validation trial.

People with intellectual disability (*n* = 48) will be invited to join one of 5 or 6 accessible workshops of approximately 10 people with intellectual disability and 2 to 3 trained support people, facilitated by members of the research team. The workshops will last approximately 2 to 3 h. Support people will be identified through Family Planning Australia networks to participate in a pre-workshop session where they will receive training according to a structured session plan on how to use the co-produced resource with people with intellectual disability. The trained support people will then use the resource with workshop participants in a way that simulates what would happen in a community setting (the intervention). Individual participants with intellectual disability will be supported to complete a brief set of pre-intervention open-ended accessible questions to assess informed decision making at the start of the workshop which will be repeated at the end of the workshop or within the next week depending on the participant’s choice. Qualitative data regarding the overall perceptions of the co-produced resource will be gathered during the workshops by the research team through audio-recording of the group discussion.

A subset of participants with intellectual disability (*n* ≈ 20 or until saturation is reached) will be invited to participate in post-intervention qualitative interviews, with the option of additional body-mapping, to provide further insights into perceptions of the resources and to support the interpretation of the study outcomes (41).

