#### Outcome measures

2.5.1

The study outcome measures align with the study aims. Triangulation of quantitative and qualitative outcome measures will be used to evaluate pre-post differences for the main trial and sub-studies. The qualitative outputs will provide insights into participants’ perceptions of the resources and facilitate the interpretation and explanation of the primary and secondary outcomes.

The primary outcome measure is informed decision-making about cervical screening by people with intellectual disability across the domains of knowledge, attitudes to screening and intention to screen, measured by an accessible modified tool (49–52). The modified tool will collect data during accessible workshops in the main trial as described in section 2.4.2. Given the lack of an existing validated tool to measure informed decision-making by people with intellectual disability about health screening, the research team led by the chief investigator with intellectual disability and health literacy experts, aims to modify an existing tool (49, 50). The tool will likely be employed using interviews to assess knowledge, attitudes and intention to screen including open-ended accessible questions around the role of screening in preventing cervical cancer, screening options, including the choice of a self-collected test, and the likely consequences of screening including recommended follow-up after an abnormal test result. Similarly, participants’ attitudes towards screening may include agreement or disagreement with accessible statements that cervical screening is ‘beneficial’ or ‘harmful,’ while intention to screen may be assessed through an accessible scale with responses ‘I will,’ ‘I am not sure,’ ‘I will not.’

Secondary outcome measures (assessed during the main trial sub-studies) are:

participation in the NCSP by people with intellectual disability, including uptake of self-collection versus clinician collection;pre-post differences in family members’ and support peoples’ health literacy, attitudes, and self-efficacy in supporting cervical screening for people with intellectual disability;pre-post differences in healthcare providers’ knowledge, attitudes, self-efficacy and preparedness in supporting and providing cervical screening for people with intellectual disability.

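### The abstract has the support people who teach the resource also help participants answer the primary-outcome questions, so in a single-arm pre-post trial prompting cannot be told apart from benefit

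*Protocol article*

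**What the plan says.** **Delivery.** In section 2.4.2 (Main trial design), "The trained support people will then use the resource with workshop participants in a way that simulates what would happen in a community setting". Each workshop has "approximately 10 people with intellectual disability and 2 to 3 trained support people, facilitated by members of the research team". The support people are trained in a session held before the workshop.

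**Help with the outcome questions.** The abstract (Methods) names the helpers: "Trained support people will provide them with the co-produced resource in accessible workshops (intervention) and support them in completing pre-post questions". Section 2.4.2 is passive on the same step: "Individual participants with intellectual disability will be supported to complete a brief set of pre-intervention open-ended accessible questions to assess informed decision making". The questions are put at the start of the workshop and then "repeated at the end of the workshop or within the next week depending on the participant’s choice".

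**The measure.** Section 2.4.2 states that "The modified tool will collect data via interviews using a brief set of pre-intervention open-ended accessible questions across three domains". Section 2.5.1 (Outcome measures) is more tentative: "The tool will likely be employed using interviews to assess knowledge, attitudes and intention to screen including open-ended accessible questions". It adds that no validated tool exists for this population. Attitudes may be captured by agreement with statements, and intention on a three-option scale. Section 2.4.3 reduces the outcome to a yes/no status, with an expected rise from 20% to 50%.

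**Scoring.** The article does not say who turns the answers into that status, by what rule, or whether that person knows the time point.

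**The concern.** The only primary contrast is post against pre in the same people. Any feature of the measurement that differs between the two occasions and favours post is counted as effect. If the abstract is followed, the helper at the post questions may have explained the same content to the same participant shortly before. That helper knows what was covered and may cue it, or may hear a partial answer as a complete one. The risk is greater where answers are open-ended. It is also greater where a participant uses augmentative and alternative communication, which the eligibility criteria allow, because the helper's interpretation may shape what is recorded. A p-value below 0.05 against zero change gives no protection. At stake is the claim of effectiveness on which the article makes national release of the resource depend.

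**Working it through.** **1. The passages side by side.** The abstract assigns delivery and question support to the trained support people. Section 2.4.2 assigns delivery to them and leaves question support unassigned. The two do not conflict, so the abstract's assignment stands as the only one stated. Section 2.1.3 has expert disability researchers conduct the qualitative interviews with this group. It does not say that this covers the primary-outcome questions.

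**2. The plan's own sample size.** Inputs from section 2.4.3: difference 0.30, SD 0.5 at each time point, zero correlation, 80% power, 5% alpha (two-sided, section 2.5.2).
- SD of the difference = √(0.5² + 0.5²) = 0.707
- n = ((1.960 + 0.842) × 0.707 / 0.30)² = 43.6, rounded up to 44, as stated.

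The calculation allows only for sampling error and has no term for measurement drift.

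**3. Effect of drift when nothing has truly changed.** Assumptions: 44 pairs, pre proportion p = 0.20, recorded post proportion q = 0.20 + b, where b is pure drift. The documents give no value for b, so 10 and 15 points are illustrative. They correspond to a net 4.4 and 6.6 of 44 participants, or a third and a half of the 30-point planned effect. For pre-post correlation ρ:
- P(yes at both) = pq + ρ√(p(1−p)q(1−q))
- P(no then yes) = q − P(yes at both); P(yes then no) = p − P(yes at both)
- McNemar statistic = (difference in discordant counts)² / (sum of discordant counts), significant above 3.84

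Summing over all possible discordant counts gives:

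| Drift b | ρ | No→yes | Yes→no | Asymptotic McNemar | Exact McNemar |
|---|---|---|---|---|---|
| 0 | 0 | 0.160 | 0.160 | 4.6% | 2.7% |
| 10 points | 0 | 0.240 | 0.140 | 19% | 13% |
| 10 points | 0.3 | 0.185 | 0.085 | 23% | 16% |
| 10 points | 0.5 | 0.148 | 0.048 | 30% | 20% |
| 15 points | 0 | 0.280 | 0.130 | 35% | 27% |
| 15 points | 0.3 | 0.223 | 0.073 | 44% | 35% |
| 15 points | 0.5 | 0.185 | 0.035 | 58% | 47% |

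**4. Cross-check on the plan's own variance.** The standard error is 0.707/√44 = 0.1066. The chance of a significant improvement is 1 − Φ(1.960 − b/0.1066). This gives 15.3% at 10 points and 29.0% at 15 points, against 2.5% in that direction with no drift.

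McNemar stands in here for the planned logistic regression (section 2.5.2). The direction of the result does not depend on that choice, but the exact percentages do.

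**The case against.** **The dual role rests on one sentence of the abstract.** This is fair. Section 2.4.2 names no helper, and section 2.1.3 leaves room for researchers to collect the data. But nothing in the main text withdraws the abstract's assignment. If other people are meant, the text needs to say so.

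**A reader might infer that answers are judged by someone who knows the time point.** The documents do not say this. They are silent on scoring, and a full protocol may settle it. Whoever collects answers in person will know the occasion, but later scoring of recorded answers could be masked.

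**A reader might infer that helpers learn the content between the two measurements.** Section 2.4.2 rules this out, because training comes before the workshop and so before both sets of questions. What differs at post is that the helper has since taught the material.

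**Two of the three domains may use closed responses.** This would confine lenient scoring mainly to the knowledge items. It does not stop prompting on the others.

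**Other safeguards exist.** Registry-linked uptake at 9 months cannot be inflated by help with the questions. The qualitative work triangulates, the trial is described as a pilot, and the Discussion admits the shift to a single arm. These limit the risk of a wrong decision but leave the primary estimate exposed. The limitations listed there do not include prompting or assessment bias.

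**Separation may be hard to staff.** If all 2 to 3 support people deliver to the whole group, none is free to help. A less familiar helper also sits awkwardly with a rapport-based approach. Both points stand, and the fix allows for them.

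**Conclusion.** The point holds as a weakness in a stated role. As the abstract has it, those who deliver the resource also help participants answer the primary-outcome questions, and a single-arm comparison cannot separate that help from benefit. With an assumed net drift of 10 points and no true change, a significant result would occur in about 19-30% of trials, and with 15 points in about 35-58%. These figures are for asymptotic McNemar with ρ from 0, the plan's own assumption, to 0.5. Exact tests give 13-20% and 27-47%. The drift sizes are assumptions, and the documents give no evidence that drift of this size will occur. On scoring, the supportable statement is only that the article describes no independent or masked scoring. The change should be made before Stage 2 starts; it is not fatal to the trial.

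**What to change.** 1. **Separate the roles.** State in the abstract and in section 2.4.2 that the primary-outcome questions are administered and supported by research-team members already at the workshop, or by a support person who did not deliver the resource to that participant. Use the same helper and a fixed prompt script before and after.
2. **Mask the scoring.** Record answers verbatim, remove the pre/post label and shuffle the records. Have an existing team member who was not at that workshop score them blind to time point, against a rubric locked beforehand.
3. **Fallback.** If the roles cannot be separated at a workshop, keep the masked scoring there and list prompting among the limitations in the Discussion.

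Masked scoring alone does not remove prompting, so both of the first two steps are needed.

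**Cost.** A rota and a data-handling step with existing staff, with no control arm, extra participants or change to 44 or 48. Some participants will be helped by a less familiar person, scoring will not be live, and the content of an answer may partly reveal its time point. The tool is still being developed and Stage 2 still awaits ethics approval and registration, so the change is cheap now.

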**Outcomes and analysis:**

Our primary outcome is a change in informed decision-making by people with intellectual disability across the domains of knowledge, attitudes, and screening intention. Secondary outcomes include: (i) uptake of screening in the 9-months following the intervention workshops, (ii) changes in health literacy, attitudes and self-efficacy of family members and support people, and (iii) changes in knowledge, attitudes, self-efficacy and preparedness of screening providers. Each participant group will evaluate acceptability, feasibility and usability of the resources.

**Discussion:**

If found to be effective and acceptable, the co-produced cervical screening resources and training materials will be made freely available through the ScreenEQUAL website to support national, and potentially international, scale-up.

## Introduction

1

In 2020 the Director General of WHO, [name], launched the Global Strategy for the Elimination of Cervical Cancer as a public health problem within the next hundred years (1). This previously unthinkable goal is achievable because of knowledge advances about the role of human papillomavirus (HPV) as the cause of almost all cervical cancers, and subsequent evolution of preventive technologies. Despite these advances, cervical cancer remains a disease of inequity, reflecting structural and psychosocial barriers to preventive care across the three pillars of HPV vaccination, cervical screening, and treatment of precancers (2, 3).

In Australia, cervical screening is provided through the National Cervical Screening Program (NCSP) with support from the National Cancer Screening Register (NCSR), which sends invitations and screening reminders to eligible people (4). In 2017 the program switched from two-yearly Pap tests from 18 to 69 years of age to five-yearly HPV tests from the 25 to 74 years (5). In 2022 a further policy change saw the introduction of universal access to self-collection of a vaginal sample without the use of a speculum, with the explicit aim of reducing screening barriers and increasing participation of under-screened people (6). As a result of these screening initiatives and the school-based HPV vaccination program, Australia is on track to eliminate cervical cancer by 2035 (7). However, elimination must be achieved equitably.

Compared with the general population, people with intellectual disability experience additional barriers to cervical screening due to stigma and discrimination, community misassumptions and non-inclusive healthcare practices (8–11). Lack of knowledge and awareness about screening and its importance in preventing cervical cancer among people with intellectual disability can result from a lack of accessible health promotion information (10, 12, 13) and the withholding of comprehensive sex education in schools, due to misplaced family and community-based fears that it may promote sexual activity or increase vulnerability to sexual abuse (14). Fears and anxiety about screening processes among people with intellectual disability can be compounded by poor clinical interactions with healthcare providers, who may lack skills and confidence to communicate effectively and to provide culturally safe screening services (15–18). De-prioritisation of screening due to competing health demands (16, 18, 19), as well as misassumptions about sexual activity and awareness of the need for screening on the part of family members, support workers and healthcare providers, are also well documented (16, 20). As pointed out by the Royal Commission into Violence, Abuse, Neglect and Exploitation of People with Disability (2023), 72% of women with intellectual disability have experienced violence since age 15 years, and 45% of women with intellectual disability have been sexually assaulted (compared with 29% of women with any type of disability) (21). These high rates of sexual trauma and assault, including child sexual abuse, experienced by people with intellectual disability compared with the general population (22), not only present an additional screening barrier, especially concerning an intimate speculum examination, but also may be overlooked as a factor determining need for screening (23).

In Australia, almost three-quarters of people who develop cervical cancer are under-screened or never-screened (24). To address screening inequities, the collection of cervical screening data through national registries to identify under-screened groups is critical. A recent national Swedish data linkage study reported very low rates of screening participation in women with intellectual disability compared with those without intellectual disability [OR 0.34 (95% CI 0.33 to 0.36)] (25). However, for most countries comprehensive data are lacking, including in Australia. The most recent peer-reviewed Australian data is from a 2010 general practice-based trial which documented screening rates as low as 10% among people with intellectual disability (26), compared to 57% in the general population at that time (27).

There is a dearth of published interventions to increase cervical screening for people with intellectual disability, and the few that exist generally have well-documented limitations including small sample sizes and limited statistical power (12, 13, 26). A randomised control trial (RCT) in the United States found that women with intellectual disability who received an educational intervention about cervical and breast screening (Women Be Healthy) did not have significantly higher rates of knowledge gain, compared with control participants (12), and subsequent modifications to the intervention yielded only a modest increase in knowledge (13). By contrast, a 2007 Australian RCT assessing the impact of a Comprehensive Health Assessment Program (CHAP) to improve interactions between adults with intellectual disability, their family member and general practitioner (GP) reported an eight-fold increase in Pap tests (95% CI 1.8–35) compared with the control group (28). However, as noted by the authors, this approach was unable to measure empowerment of family members and people with intellectual disability (26, 28).

This paper outlines the protocol of ScreenEQUAL, a co-designed two-stage mixed-methods study, which will be carried out over 3 years by a multi-disciplinary team comprised of expert disability researchers including a chief investigator with intellectual disability, clinician researchers and health promotion experts. It will complement the CHAP which in 2023, after further modifications, was implemented nationally through a joint Department of Health and Ageing and National Disability Insurance Scheme (NDIS) initiative (29). The ScreenEQUAL program of work, like the CHAP, aligns with the Australian government’s 2021–2023 National Roadmap for Improving the Health of People with Intellectual Disability (30), which aims to address serious health inequities faced by this group.

The primary aim of ScreenEQUAL is to evaluate the effectiveness of a co-produced accessible multimodal cervical screening information resource in supporting informed decision-making about screening by people with intellectual disability. In this study, ‘informed decision-making’ refers to meeting three criteria. First, the person is given information that makes sense to them. Second, the decision is not influenced or forced. Third, the person must have capacity to make the decision (31, 32). To ensure valid consent, this process must be adjusted to fit the person’s needs so they can understand and express themselves well. Capacity refers to being able to agree to a medical treatment knowing what it involves (33). The Mental Capacity Act outlines that “a person must be assumed to have capacity unless it is established that he lacks capacity,” and that incapacity can only be established if “all practicable steps” to support capacity have been attempted without success (34).

The secondary aims are to assess:

uptake of cervical screening by participants with intellectual disability in the nine-months following the trial measured through data linkage;changes in health literacy, attitudes and self-efficacy of family members and support people in supporting cervical screening participation by people with intellectual disability;changes in knowledge, attitudes, self-efficacy and preparedness of healthcare providers in supporting and providing cervical screening for people with intellectual disability.

The objectives of Stage 1 of the study are to build on existing Family Planning Australia resources by (35):

qualitatively exploring cervical screening facilitators and barriers for people with intellectual disability as perceived by people with intellectual disability themselves, their family members and support people, healthcare providers and disability sector stakeholders;co-producing an accessible information resource to support cervical screening, including the option of self-collection, for people with intellectual disability;co-producing accompanying supporting materials for families and support people to use when sharing the accessible screening resource with people with intellectual disability;co-producing trauma-informed training materials for healthcare providers.

The Stage 2 objectives are to evaluate the co-produced study outputs (b,c,d) through a single-arm main trial with participants with intellectual disability, and single-arm sub-studies with family members and support people, and healthcare providers.

Figures 1, 2 provide an overview of Stages 1 and 2 of the study, and the study timeline is shown in Figure 3.

